## Abstract

**Background:**

Music therapy is one of the most frequently used complementary therapies in different palliative care settings. Despite its long tradition and high acceptance by other health-care professionals, evidence on the effectiveness of music therapy interventions for terminally ill patients is rare. Recent reviews and health-care reports consistently point out the need of music therapists to provide an evidence-based rationale for their clinical treatments in this field. Therefore, the present study evaluates the psychological and physiological response of palliative care patients to a standardized music therapy relaxation intervention in a randomized controlled trial.

**Methods/design:**

A sample of 84 participants from a palliative care unit in Heidelberg is randomized to either two sessions of music therapy or two sessions of a verbal relaxation exercise, each lasting 30 minutes. The music therapy sessions consist of live played monochord music and a vocal improvisation, the control group uses a prerecorded excerpt from the mindfulness-based stress reduction program containing no musical elements. Outcome measures include self-report data on subjective relaxation, well-being, pain intensity, and quality of life, as well as continuous recording of heart rate variability and blood volume pulse as indicators of autonomous nervous system functioning.

**Discussion:**

To our knowledge, this study is the first clinical trial in Europe and one of very few randomized controlled trials worldwide to systematically examine the effects of music therapy in palliative care.

**Trial registration:**

German Clinical Trials Register – DRKS00006137

## Background

For more than 35 years, music therapists have been working in different settings of end-of-life care. The Canadian music therapist, Susan Munro, was the first to systematically describe the physical, psychological, social, and spiritual impact of her work with terminally ill patients at the world’s first palliative care unit, founded by Balfour Mount in Montréal [1]. Since then, music therapy has become a substantial part of multidisciplinary palliative care in many industrialized countries. Today, music therapy is one of the most frequently used complementary therapies in US hospices, and is widely accepted by other professional groups in the UK [2, 3]. The German classification of procedures (OPS 8-982 and OPS 8-98e) explicitly recommends the use of music therapy in inpatient and outpatient palliative care treatment [4].

Music therapy is defined as “a systematic process of intervention wherein the therapist helps the client to promote health, using music experiences and the relationships that develop through them as dynamic forces of change” [5]. In clinical palliative care practice, music therapy generally aims at the improvement or maintenance of the patient’s quality of life, including the management of pain and stress, the regulation of negative emotions (e.g. anxiety, anger, and depression), as well as the facilitation of communication and spiritual experiences [6]. Music therapy techniques can be categorized as either active (in case the patient actively participates in the production or reproduction of music) or receptive (where the patient listens to live or prerecorded music). In end-of-life care, techniques typically encompass relaxation or imaginative interventions (receptive), the therapeutic use of songs (active or receptive), and various forms of improvisation (active). Verbal conversation can proceed or complement music therapy interventions but is not an inherent prerequisite for the accomplishment of a music therapeutic contact [7]. In most cases, the interventions are tailored according to the patient’s physical state and psychosocial needs.

Despite its long tradition and positive clinical experiences, limited evidence is available on the effects of music therapy in end-of-life care. The 2010 Cochrane review^a^ included only five trials that implemented (quasi-)randomized controlled designs [8]. Mixed findings emerged with regard to QOL as a study outcome. While Hilliard [9] reports a significant improvement of QOL through music therapy compared to standard care alone, Nguyen [10] did not find a significant effect, supposedly due to a very small sample size. Music therapy has been associated with a reduction of pain [11–14] and anxiety [10, 15], in addition enhancing communication [16] and spiritual well-being [17]. Interestingly, one study [18] reported a decrease in salivary cortisol levels of nine participants after a receptive music therapy session, while other physiological (heart rate, respiration rate) or objective outcomes (e.g. days of survival) did not show significant differences or changes over time [9, 15, 19]. However, many of these results must be interpreted with caution as they stem from studies with high risk of bias due to small sample sizes, missing control group conditions or randomization procedures, as well as inadequate statistical analysis and reporting of data. A review of qualitative findings emphasizes the meaningfulness and important role of music therapy not only for patients, but also for family caregivers and staff members [20].

Although the abovementioned studies suggest that there might be a beneficial effect of music therapy on outcomes relevant for end-of-life care, the decision of how (and whether) to apply music therapy still vastly relies on subjective presumptions and clinical expertise. Current reviews consistently attest a lack of high quality studies, ruling out the possibility to provide an evidence-based recommendation in favor or against the use of music therapy within the field of palliative care [8, 21].

Hence, the general aim of the present study is to improve the body of research on this important but underrepresented topic. More precisely, the study goals are to evaluate the effectiveness of a music therapy relaxation intervention regarding palliative care patients’subjective perception of relaxation, well-being, and pain (i.e. immediate effects on psychological outcomes; primary outcome of this study),autonomous relaxation response indexed by HRV and BVP (i.e. immediate effects on physiological outcomes),health-related quality of life (i.e. medium-term effects).

Therefore, we compare the effects of music therapy to the ones of a control group, using a prerecorded mindfulness exercise without musical elements or therapeutic interaction. We hypothesize improvements over time in both groups, but a superiority of the music therapy intervention on all three aforementioned dimensions.

## Methods/design

The following sections present the details of the research methodology designed to address these objectives. The presented study protocol received IRB approval by the Ethics Committee of the Medical Faculty of Heidelberg University on January 3^rd^ 2013 (S-406/2012).

### Participants and setting

The present study is a collaborative research project in cooperation of the Centre of Pain Therapy and Palliative Care Medicine at the University Hospital Heidelberg and the School of Therapeutic Sciences at the SRH University Heidelberg. Recruitment, interventions, and data collection are carried out at the palliative care unit of the St. Vincentius Hospital in Heidelberg, Germany. All patients are assessed for eligibility according to predefined inclusion and exclusion criteria listed in Table 1.

**Tables 1 Tab1:** **Inclusion and exclusion criteria**

Inclusion criteria	Exclusion criteria
Palliative care according to OPS 8-892	Terminal phase
Sufficient understanding of German or English language	Cognitive impairments (e.g. brain metastases, ICD 10: C71, C72)
	Apallic syndrome (ICD 10: G93.80)
	Deafness (ICD 10: H90, H91)
	Restlessness and agitation (ICD 10: R45.1)

### Study design and procedures

The study is designed as a prospective RCT with two parallel arms. Hospitalized patients eligible for study inclusion are contacted at bedside in their rooms and informed about the procedures and objectives of the study. The investigator presents the purpose of the study as to compare the effects and feasibility of two commonly used relaxation interventions for the palliative care context. No information is given about which of the two interventions is the actual experimental condition. If patients agree to participate, the investigator asks them to sign the informed consent sheet, and baseline assessment of the patients’ QOL and previous experience with relaxation techniques is obtained. Following that, the investigator gathers relevant information from the patients’ medical record and opens a serially numbered opaque envelope containing assignment to one of the two study arms (see interventions). We used a computer-based block permutation for the generation of the randomization sequence before the onset of the study. The investigator then returns to the patients’ room with the physiological measuring devices, collects pretest data on relaxation, well-being, and pain using VAS, and starts a 5-minute pretest recording of HRV. Then, either the experimental condition (music therapy) or the control condition (verbal relaxation) is initiated, lasting for twenty minutes. HRV is recorded throughout this procedure. Data collection is complemented by another five minutes of HRV recording and posttest VAS assessment following the intervention. The entire procedure lasts thirty minutes and is repeated two days later, finishing with the follow-up assessment of patients’ QOL. In both groups, the patient rests in a supine position for the entire duration of the session. Figure 1 shows a flow diagram of the study design and procedures.

**Figure 1 Fig1:**
[figure not shown]
**Study design and procedures.**

### Interventions

Patients are randomly assigned to either a music therapy relaxation intervention or a verbal relaxation intervention.

#### Music therapy

The experimental condition is carried out by a professional music therapist with several years of working experience in end-of-life care. The music therapy relaxation technique combines a verbal introduction, soothing sounds played live on a monochord and vocal improvisation. The monochord is designed for the use in therapeutic contexts. Twenty-one equally tuned strings and 3 bass strings are placed on a rectangular wooden corpus. A slow and even play of the strings creates a full and atmospheric monochrome sound that is perceived as calming or relaxing. A recent qualitative study found the body tambura (an instrument with similar characteristics) to elicit pleasant images and visualizations in palliative care patients [22]. A pilot EEG study with oncological patients showed that monochord music may be associated with an increase in posterior theta activity and a decrease in alpha band and mid-frontal beta-2 band activity, most likely reflecting a relaxation response [23]. In another pilot study, patients in oncological rehabilitation reported to be more balanced, less nervous, and less exhausted after listening to monochord music [24].

After the HRV pretest recording, the experimenter leaves the room for the remainder of the intervention. The music therapist briefly explains the process and principle of the intervention. The actual treatment starts with a brief body scan and breathing exercise accompanied by low and gentle sounds on the monochord. The therapist then initiates a vocal improvisation in an ionian or mixolydian mode and raises volume and dynamics of the musical play, adapted to the patient’s breathing. After 10 minutes, the improvisation reaches its peak and the therapist gradually and slowly reduces the musical parameters of the instrumental and vocal play. The patient is asked, gently to return his or her attention to the present situation. A brief feedback conversation gives the participant the opportunity to reflect on his experiences during the music therapy intervention. After another five minutes, the therapist leaves the room and the investigator returns for posttest outcome assessment and debriefing.

#### Verbal relaxation

The verbal relaxation intervention uses a 20-minute excerpt from Jon Kabat-Zinn and Ulrike Grossmann’s CD “Stressbewältigung durch die Praxis der Achtsamkeit”^b^
[25], adopted from the *mindfulness-based stress reduction* (MBSR) program. MBSR is a structured 8–10 weeks group program that has shown to effectively improve the physical and mental health of participants from different medical and non-medical contexts by training participants’ self-awareness and mindfulness [26].

The control condition’s time-frame is identical to the experimental condition (5 min. baseline → 20 min. intervention → 5 min. postline). The standardized application of the intervention utilizes a conventional MP3 player and stereo headphones and therefore, requires no additional personnel. The investigator stays silently inside the room, in case the patient expresses unease or wants to cancel the intervention. The prerecorded MBSR track lasts twenty minutes and contains a body scan and breathing exercise, spoken by a soft, female voice. After completion, the investigator asks the participant to remain in his position for the 5-minute posttest HRV recording and VAS assessment.

Figure 2 provides an overview of the procedures and time course of the experimental and control condition.

**Figure 2 Fig2:**
[figure not shown]
**Intervention procedures and time course.**

### Outcomes

#### VAS (primary outcome)

Patients’ subjective experience of immediate short-time effects of the intervention is measured via three different VAS, assessing relaxation *(-5 = “very tense”* to *+5 = “very relaxed”)*, general well-being *(−5 = very bad* to *+5 = very good)*, and pain intensity *(0 = no pain at all* to *10 = worst pain possible)*. The scales’ endpoints depict good vs. bad smileys and a color code from red to green for better visualization of the valences. Subjective ratings are assessed immediately before and after each session.

#### HRV/BVP

During the 30-minutes intervention we collect continuous data on the intervals between successive heartbeats in milliseconds (i.e. HRV). For reason of feasibility and lower patient burden, we decided to use a BVP finger sensor with a sampling rate of 128 SPS for the least invasive signal processing, instead of a high-resolution ECG signal that would require electrode placement. A NeXus-16® interface sends the BVP signal to the BioTrace + ® software on a laptop computer via Bluetooth. BioTrace® records raw data of all sessions and exports IBI text files for each participant and session. Kubios v2.1® transforms these tables into HRV parameters based on six successive 5-minutes-samples for further statistical analyses with IBM SPSS Statistics 20®.

Despite the derivation of HRV parameters, BVP signals offer the possibility to measure vasodilation/vasoconstriction as a second set of markers on autonomous functioning. A shift to parasympathetic dominance is expected to manifest in an increase in the BVP amplitude. In accordance to the HRV analysis, we will calculate mean values and standard deviations for 5-minutes-intervals for each patient and subject.

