### Data analysis

#### Sample size calculation

Statistical power calculations for this study are adjusted for immediate short-time effects on self-report VAS data (i.e. the primary outcome). Bradt and Dileo’s [8] findings suggest that medium sized effects are most likely to be expected for the impact of music therapy on psychosocial outcomes in palliative care. Recent articles [29, 30] on sample size calculations emphasize the superiority of ANCOVA models for analyzing the results of randomized, controlled trials over the repeated-measures ANOVA approach. The inclusion of pretest values as a covariate in these models increases statistical power (i.e., the likelihood to identify statistically significant effects).

Assuming statistical power of (1-β) = .80, type-I error probability of α = .05, and a correlation between covariate and outcome of ρ = .6, a total sample size of *N* = 84 is required to detect medium sized effects between groups [29]. With an expected drop-out rate of 10%, approximately 92 participants need to be recruited for this study. The risk of attrition bias will be addressed in the course of intention-to-treat analyses.

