#### Statistical analyses

We will test for significant differences between groups at baseline using independent samples t-tests, with α = .20 to reduce type-II error probability. For all study hypotheses tests, type-I error probability is set to α = .05. VAS and QOL data will be analyzed with ANCOVA models, where posttest values serve as criteria, pretest scores as covariates and group assignment as a fixed predictor, respectively. We will run repeated-measures ANOVA on physiological data (HRV/BVP) to test for polynomial trends over time, main effects of group allocation, and interaction effects.

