The research methodology of this study contains some trade-offs and subjective decisions that were discussed intensively in our team (e.g. the decision for a less precise but also less invasive method of HRV measurement). We are confident to have set up a both ethically justifiable and feasible research design that provides high methodological rigor capable of producing valid and reproducible results. To our present knowledge, this study will be the first European RCT on the effects of music therapy in palliative care.

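### If the BioTrace export locates beats at the 128 SPS sample points, HRV carries an avoidable timing error of about 3.2 ms per interval and 5.5 ms per successive difference; interpolating the stored waveform would remove most of it

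*Protocol article*

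**What the plan says.** The HRV/BVP part of the Outcomes section sets out the measurement chain step by step.

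- The quantity collected is "continuous data on the intervals between successive heartbeats in milliseconds (i.e. HRV".
- The source is a "BVP finger sensor with a sampling rate of 128 SPS for the least invasive signal processing", chosen for feasibility and lower burden "instead of a high-resolution ECG signal that would require electrode placement".
- On storage and export, "BioTrace® records raw data of all sessions and exports IBI text files for each participant and session".
- On processing, "Kubios v2.1® transforms these tables into HRV parameters based on six successive 5-minutes-samples".

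Kubios therefore receives intervals, not the waveform. The article names no HRV parameter and does not say whether pulse peaks are interpolated before the intervals are formed.

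Under Statistical analyses, "We will run repeated-measures ANOVA on physiological data (HRV/BVP) to test for polynomial trends over time", with group main effects and interactions. The Discussion lists among its trade-offs "the decision for a less precise but also less invasive method of HRV measurement", without giving a size for the loss.

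**The concern.** Short-term HRV is computed from small differences between beat times, so the precision of those times matters more than it would for mean heart rate. A pulse signal sampled 128 times a second has a sample every 7.8 ms. If a beat is placed at the nearest sample, that rounding goes into the interval file, and Kubios cannot undo it because it never sees the waveform.

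At stake is the autonomic relaxation objective, one of three dimensions on which the article hypothesises superiority of music therapy. Rounding error acts as a noise floor: it raises observed HRV and compresses true changes, proportionally more where HRV is low. The patient gains nothing from the loss. Sparing the electrodes requires the finger sensor; it does not require reading beat times off the sample grid.

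**Working it through.** **The plan's own figure.** The only power figure is N = 84, for the VAS outcome ("Assuming statistical power of (1-β) = .80", α = .05, ρ = .6, medium effect, taken here as d = 0.5, two-sided). The normal approximation gives 2 × (1.96 + 0.84)² / 0.25 × (1 − 0.36) = 40.2, so 41 per arm or 82 in total. With the noncentral t distribution, power is 0.798 at N = 82 and 0.808 at N = 84. The figure reproduces and does not depend on HRV. The article states no figure for timing error, so what follows is a new calculation.

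**Inputs.** Sampling rate 128 per second (HRV/BVP section). Assumption: the export places each beat at a sample point. RMSSD levels of 5 to 30 ms are an assumed range.

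**Error size.**

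- Sample spacing: T = 1000/128 = 7.8125 ms.
- One beat time, uniform rounding error: variance T²/12 = 5.09 ms², SD 2.26 ms.
- One interval (difference of two beat times): variance 2 × 5.09 = 10.2 ms², SD 3.19 ms. This is the noise that enters SDNN.
- One successive difference (beat times weighted 1, −2, 1): variance 6 × 5.09 = 30.5 ms², SD 5.52 ms. This is the noise that enters RMSSD.

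**Effect on RMSSD.** Observed = √(true² + 30.5). The error adds in quadrature, so the net excess shrinks as true RMSSD grows. The table follows a true 20% rise.

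| True RMSSD (ms) | Observed, formula | Observed, simulation | Change kept, raw scale | Change kept, log scale |
|---|---|---|---|---|
| 5 | 7.45 | 7.41 | 0.70 of 1.00 ms (70%) | 50% |
| 10 | 11.42 | 11.41 | 1.79 of 2.00 ms (89%) | 80% |
| 20 | 20.75 | 20.64 | 3.88 of 4.00 ms (97%) | 94% |
| 30 | 30.50 | 30.39 | 5.92 of 6.00 ms (99%) | 97% |

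The simulation used 375 beats per 5-minute window, autocorrelated intervals with mean about 800 ms, and 400 runs per setting. At a true RMSSD of 15 ms the formula gives 15.98 ms, an excess of about 1 ms. Below that level the distortion grows quickly.

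**Effect on SDNN.** In the same simulation, true SDNN of about 5, 10 and 20 ms was observed as 5.90, 10.46 and 20.16 ms, a smaller distortion than for RMSSD.

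**Effect on the test.** Compression of a mean change is not the same as loss of power, because variation between patients is compressed too. An illustrative simulation compared the post-minus-pre change in 42 patients per arm, with a 20% rise in one arm, between-patient log-SD of 0.4 to 0.6 and within-patient log-SD of 0.3 (all assumed). Raw-scale power moved as follows:

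- median RMSSD 20 ms: 0.67 to 0.67, and 0.61 to 0.59;
- median 10 ms: 0.68 to 0.65, and 0.60 to 0.55;
- median 5 ms: 0.68 to 0.57, and 0.60 to 0.49.

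The size depends on how the variation is modelled. If 0.3 is taken as the log-SD of the change itself and the quadrature formula is applied to each value, the 5 ms losses are smaller: 0.74 to 0.69, and 0.66 to 0.58.

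**After interpolation.** With an effective grid eight times finer (assumed; 0.98 ms), the successive-difference error falls from 5.52 to 5.52/8 = 0.69 ms. In simulation a true RMSSD of 5 ms is then observed as 5.05 ms.

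**The case against.** The strongest objection is that the premise is not in the document. A sampling rate does not show where the software places a beat; if BioTrace already interpolates its peaks, most of the error disappears. This stands, and it makes the point conditional. It can be settled by looking at one exported file.

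Second, peak detection is the kind of detail an article may leave to a fuller document, and the article openly concedes lower precision. This stands in part. Silence on interpolation is not itself a fault. But the article does state the chain from sensor to export to Kubios, and as stated that chain has no step where precision lost at beat detection could be recovered. The concession in the Discussion defends the finger sensor against ECG electrodes, which is not disputed here. It does not bear on how beats are read from the stored signal.

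Third, a reader might infer several stronger claims that the document does not support:

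- *Every HRV window is inflated by 5.5 ms.* The error adds in quadrature, so the net excess is about 2.5, 1.4 and 0.75 ms at true RMSSD of 5, 10 and 20 ms. The 5.5 ms applies to successive-difference measures only, and none is named. BVP amplitude does not use beat timing.
- *Half of a true effect is lost.* That is the log-scale figure at 5 ms. The article states no log transformation; the raw-scale figure is 70% kept.
- *These patients have very low HRV, so a false null is likely.* The article gives no HRV level. The illustrative power loss is at most about 5 points at a median of 10 ms or more, and reaches about 11 only near 5 ms.

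**Conclusion.** The point holds as a conditional, inexpensive improvement to a non-primary outcome. If the exported intervals lie on the sample grid, timing error is about 3.2 ms per interval and 5.5 ms per successive difference. The distortion of RMSSD is material at roughly 15 ms or below and slight above that.

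Because the rounding does not depend on arm, it attenuates differences and cannot create one. The VAS primary outcome and N = 84 are unaffected.

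The conclusion rests on two things the article does not give: how BioTrace places beats, and the HRV level of the patients. The calculation covers sampling error alone, not other limits of a finger pulse signal. Nothing is lost irrecoverably, because the raw data of all sessions are recorded.

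**What to change.** 1. Check the export before any analysis by arm. See whether the intervals fall on multiples of 7.8125 ms, allowing for rounding in the file. Near 800 ms, for example, grid values would be 102, 103 and 104 × 7.8125 = 796.9, 804.7 and 812.5 ms, with nothing between.
2. If they do, derive beat times from the stored raw BVP waveform by spline up-sampling (for example to 1000 Hz) or by parabolic interpolation around each pulse peak. Apply one script to all sessions, identically in both arms and blind to arm, and pass these interval tables to Kubios in place of the direct export.
3. If they do not, record that the export already interpolates, and leave the chain as it is.
4. State in the plan which route was taken.

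Cost: one extra scripted processing step and some data handling. There is no new device, no new recording and no added burden on patients.

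### BVP amplitude is to be tested without baseline adjustment, and the planned group main effect is a weak test of an expected within-patient increase

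*Protocol article*

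**What the plan says.** The outcomes section (HRV/BVP) records the signal with a finger sensor: "we decided to use a BVP finger sensor with a sampling rate of 128 SPS". It gives no unit, calibration or variance for the amplitude. The hypothesis is directional and concerns change: "A shift to parasympathetic dominance is expected to manifest in an increase in the BVP amplitude". The summary measure follows the HRV analysis, which uses "six successive 5-minutes-samples": for BVP, "we will calculate mean values and standard deviations for 5-minutes-intervals for each patient and subject". No ratio, log or baseline reference is mentioned.

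The statistical analyses section puts HRV and BVP into a repeated-measures ANOVA "to test for polynomial trends over time, main effects of group allocation, and interaction effects". In the same paragraph, ANCOVA with the pretest score as covariate is reserved for VAS and QOL.

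Two other places bear on this:
- The time course of each session, identical in both arms, is "5 min. baseline → 20 min. intervention → 5 min. postline", so a pre-intervention window always exists.
- The sample size section cites recent articles for the superiority of ANCOVA over repeated-measures ANOVA in randomised trials, and says that the pretest covariate raises power.

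**The concern.** The hypothesis is about a rise from the patient's own starting level. The group main effect instead compares average levels between patients. If all six windows enter the model, that average includes the window before any treatment. Differences in level that have nothing to do with treatment then go straight into the error term.

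The group-by-time interaction does better, because each patient serves as own control. However, subtraction removes additive differences only. If patients differ by a multiplicative factor, the same percentage rise yields a larger raw change in a patient with a strong signal, and a few such patients dominate the variance.

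At stake is power for the second autonomic marker. A true difference could be missed more often than the design requires. The article gives BVP the approach that its own sample size section ranks lower, although the data needed for the better one are already recorded.

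**Working it through.** **1. The plan's own figure.** The article gives no power figure for BVP, only N = 84 for the VAS. Inputs: power 0.80, alpha 0.05 (two-sided assumed), correlation 0.6, medium effect taken as d = 0.5, equal allocation assumed.

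n per arm = 2 × (1.96 + 0.8416)² × (1 − 0.6²) / 0.5² = 2 × 7.849 × 0.64 / 0.25 = 40.2, so 41 per arm and 82 in total. One extra per arm as a small-sample correction gives 84. Noncentral-t ANCOVA power at 84 is 0.808. The figure reproduces, and the BVP check uses 84 / 2 = 42 per arm.

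**2. Assumptions for BVP (none is in the article).**
- Each patient has a gain that is lognormal with log SD s.
- Amplitude before and after is gain times lognormal noise, with a log SD of change of 0.3, so the noise variance per window is 0.3² / 2 = 0.045.
- The music arm's later amplitude is multiplied by exp(0.18) = 1.20.

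**3. Log scale, by formula.** For the log ratio to baseline the standardised effect is 0.18 / 0.3 = 0.6, whatever s is. The noncentrality is 0.6 × √(42/2) = 2.75 on 82 df, so power is 0.78.

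For log amplitude with log baseline as covariate, ρ = s² / (s² + 0.045) and the residual SD is √[(s² + 0.045)(1 − ρ²)].
- s = 0.4: ρ = 0.78, SD 0.283, power 0.82.
- s = 1.0: ρ = 0.957, SD 0.297, power 0.78.

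**4. All analyses, by simulation** (6000 replicates per row, Monte Carlo error about 0.01):

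| s | raw, baseline and later averaged | raw, later only | raw change | raw ANCOVA | log ratio | log ANCOVA |
|---|---|---|---|---|---|---|
| 0.2 | 0.39 | 0.78 | 0.78 | 0.86 | 0.77 | 0.88 |
| 0.4 | 0.15 | 0.40 | 0.74 | 0.75 | 0.77 | 0.82 |
| 0.6 | 0.09 | 0.21 | 0.65 | 0.65 | 0.78 | 0.80 |
| 0.8 | 0.07 | 0.13 | 0.55 | 0.56 | 0.78 | 0.78 |
| 1.0 | 0.05 | 0.09 | 0.44 | 0.45 | 0.77 | 0.77 |

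With no true effect, every column rejects in about 0.04 to 0.06 of replicates.

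The reason is simple arithmetic. At s = 1.0 a patient one SD above the median has exp(1) = 2.72 times the median patient's raw change for the same percentage rise.

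**5. Six-window model.** The two-window average gives the baseline half the weight, which is harsher than one window in six. A separate simulation therefore used six windows, a 20% against a 10% rise, an SD of individual response of 15%, interval noise of 5%, 42 per arm and 1500 runs.

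| CV of multiplicative gain | raw group main effect | raw linear group-by-time | same contrast on log |
|---|---|---|---|
| 0.01 | 0.84 | 0.83 | 0.82 |
| 0.3 | 0.13 | 0.74 | 0.78 |
| 0.5 | 0.07 | 0.65 | 0.80 |
| 0.8 | 0.07 | 0.50 | 0.80 |
| 1.0 | 0.05 | 0.43 | 0.79 |

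With additive patient offsets instead (CV 0.3, 0.5, 1.0), the raw interaction keeps 0.79, 0.82 and 0.81. The raw main effect still falls to 0.13, 0.09 and 0.05. The weakness of the main effect therefore does not depend on the multiplicative assumption. The loss in the interaction does.

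**The case against.** The strongest case for the plan has four parts.

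- **The within-patient test is already there.** The ANOVA includes time trends and the group-by-time interaction, and the article does not name the group main effect as decisive. This stands. It is why the defect is a loss of power in one test and a poor choice of another, not the absence of a valid test.
- **Multiplicative gain is not in the documents.** The article is silent on unit, calibration, skin and contact. This also stands, so the size can only be shown over a range. With additive differences the raw interaction loses nothing. At s = 0.2 the raw change (0.78) matches the log ratio (0.77), and raw ANCOVA (0.86) nearly matches log ANCOVA (0.88).
- **An article condenses.** Scaling or transformation may sit in a fuller document. In part this stands: the sentence does not exclude a transformation. But the article does state both the summary and the model, and it assigns baseline adjustment to VAS and QOL only. The point concerns that stated choice.
- **The outcome is not primary.** True, and it limits the weight of the point.

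A reader might go further and infer that sensor and skin differences swamp the vasodilation effect, or that a null BVP result would be purely technical. The documents do not support this. The interaction keeps roughly 0.43 to 0.74 power over most of the assumed range, and no figure in the article fixes where in that range the trial lies.

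**Conclusion.** The point holds as a matter of efficiency and of which test answers the hypothesis. The unadjusted group main effect is a poor test of a within-patient increase whenever patients differ appreciably in level, by a factor or by an offset. Under multiplicative differences with log SD 0.4 to 1.0 its power is about 0.15 to 0.05 (baseline and later averaged). The raw change or interaction then has about 0.74 to 0.44, against about 0.82 to 0.78 for baseline-adjusted log amplitude.

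These figures rest on an assumed 1.20-fold effect, a log SD of change of 0.3 and 42 per arm. The interaction's loss from the raw unit is small if gain variation is small, and absent if differences are additive.

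It would also be wrong to infer bias or false positives: type I error stays near 0.05. The VAS primary outcome and N = 84 are untouched. The change is worth making because it is nearly free, but nothing central depends on it.

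**What to change.** In the HRV/BVP outcome text, define the BVP endpoint for each session as log mean amplitude in the 5-minute windows after baseline. In the statistical analyses section, enter that session's log baseline amplitude as covariate. Name the baseline-adjusted group effect, or group-by-time on the log scale, as the test of the BVP hypothesis. Do not use the group main effect on unadjusted amplitude that includes the baseline window for that purpose.

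Log ANCOVA is preferred to a plain log ratio because it was at least as powerful in every row of the table (0.88 against 0.77 at s = 0.2, equal at s = 1.0).

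The cost is two sentences and a transformation of data already recorded. Sessions with an unusable baseline window drop out of the BVP analysis, so their number should be reported by arm. Results will be expressed as ratios rather than in sensor units.
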